The primary aim of this study will be to evaluate whether BT increases the proportion of patients achieving the Minimal Clinically Important Difference (MCID) as measured by the Fibromyalgia Impact Questionnaire (FIQ), compared to standard care. Secondary aims will be a) the assessment of BT additional effects on pain, quality of life, anxiety and depression, b) the persistence of clinical efficacy over a six-week follow-up, c) the tolerability of BT by recording all adverse events, their severity and possible relationship with the therapy.

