### Interventions and study arms

This study consists of two parallel cohorts:BT Cohort (BTC): Patients will receive a cycle of bath or of mud-bath therapy once daily for 12 days in addition to their usual treatments for FS (see below). The thermal treatment cycle will include one session per day for a total of two weeks, with a break between the fifth and seventh day to prevent the onset of a thermal crisis. This protocol aligns with current practices and is endorsed by the Italian National Health Service which covers a cycle of a 12-day treatments, once a year for patients with rheumatic diseases such as FS. The mineral thermal baths will be carried out in a single tub or in a pool, with a duration of 10 min at a temperature of 37–38° C. The thermal mud will be applied to the skin according to standardized methods, with a duration of 15–20 min, at temperatures ranging between 40–45° C. A rest period of about 20–30 min will follow BT treatment. The whole treatment duration will last 1 h, approximately. Only muds and baths belonging to the classes of sulfurous, bicarbonate, chloride-sodium, sulphate and arsenical-ferruginous waters—according to the classification of Marotta and Sica (1933), will be allowed.Control Cohort (SCC): This group will include patients who will refuse the BT for personal reasons. Patients will continue their established routinely care for FS.

The usual care treatment will correspond to pharmacological and non-pharmacological therapies as reported in EULAR guidelines (Macfarlane et al. 2016). The intervention program must have already been stabilized for at least 3 months before the start of the study. During the study period, the patient can modify the therapy if necessary; this change will be reported.

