##### Tolerability

All adverse events, whether reported spontaneously by the patients or observed by the physician, will be reported in the personal record noting the severity. The adverse event will be considered related to the treatment if it appears after the start of the therapy or if it was known as a BT side effect. In addition, side effects related to drug therapy will be monitored and reported as part of the study.

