### Follow up

Following enrollment, each patient will be examined for 3 consecutive times; at baseline (T0), after 2 weeks (T1), and after 45 days (T2) (one month after the end of the cycle of the therapy for the BT Cohort) (Fig. 1). T0 and T1 visits will be carried out by the physician in the enrollment setting. The T2 visit will be carried-out by phone. The study will be considered concluded when all follow-up data for each patient will be collected.

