### Sample size

The primary outcome is the modification of the FIQ total score, whose minimum clinically relevant difference is 14% as compared to its initial value (Burckhardt et al. 1991). We expect a decrease in the FIQ total score of at least 14% in the 30% of the control cohort and 45% in the BT cohort. A number of 217 patients per group allows estimating an absolute difference of 15% (45—30%) in the incidence of the primary outcome between the two cohorts at an alpha level = 0.05 and with a power of 90% (Pearson’s chi-squared test). Assuming a loss to follow-up of 20%, 260 (217 + 43) patients will be enrolled per group, for a total of 520 patients.

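### The relatedness rule labels every adverse event after the start of balneotherapy as related, so the related-event rate in the BT cohort is only its all-cause post-start rate

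*Protocol article*

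**What the plan says.** Secondary aim c, at the end of the Introduction, is to assess "the tolerability of BT by recording all adverse events, their severity and possible relationship with the therapy". So attribution to BT is part of the aim, in addition to the counting of events.

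The Tolerability section sets out how this is done:

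- Capture: "All adverse events, whether reported spontaneously by the patients or observed by the physician, will be reported in the personal record noting the severity".
- Attribution: an event is "considered related to the treatment if it appears after the start of the therapy or if it was known as a BT side effect".
- Drug effects: "In addition, side effects related to drug therapy will be monitored and reported as part of the study".

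Three other statements decide which events the attribution rule will meet. Under Interventions and study arms, BT is given "in addition to their usual treatments for FS", and "During the study period, the patient can modify the therapy if necessary; this change will be reported". Under Follow up, the last contact is "after 45 days (T2) (one month after the end of the cycle of the therapy for the BT Cohort". The control cohort consists of patients who decline BT.

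**The concern.** A causality rule has to divide the events seen after treatment starts into those that the treatment may have caused and those that it probably did not. This rule accepts time order alone as sufficient, so it makes no such division.

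The setting makes that costly. The Introduction describes fibromyalgia as a persistent condition with widespread pain, fatigue, poor sleep, headache and bowel symptoms. Patients stay on their usual drugs, which may change during the study. Observation continues for about a month after the last session. Background events are therefore likely after BT start, and each one that is recorded would be counted as a BT effect.

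At stake is the related-event rate, which readers are likely to take as the safety result. The Discussion expects the study to confirm good tolerability in a large sample, and a rate that absorbs every background event cannot be used to judge that.

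**Working it through.** The article states no adverse-event rate or related-event figure, so there is nothing to reproduce. The check is one of logic, followed by an illustration with assumed rates.

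**1. The rule as written.** Let A = onset after the start of therapy and K = known BT side effect. The rule is: related = A or K.

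- Any post-start event in the BT cohort has A true, so it is related whatever K is. A true reaction is always labelled (sensitivity 100%). A background event is always labelled too (specificity 0%).
- K can change the result only where A is false: an event that began before BT, or an event in a patient who never started BT. BT can have caused neither. The second condition can therefore add only false attributions.

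**2. Against the drug sentence.** A drug side effect that begins after BT start has A true, so it is BT-related. The next sentence of the same section treats drug side effects as a category of their own. The same event then belongs to both, and the article gives no way to choose.

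**3. Against the follow-up schedule.** The rule has no closing time. An event near day 45, about 30 days after the last session, meets A just as an event on the day of a bath does.

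**4. Illustration.** Inputs: n = 260 enrolled per cohort (Sample size: "260 (217 + 43) patients will be enrolled per group, for a total of 520 patients"); b = risk of at least one background event after BT start; r = risk of at least one true BT reaction. Both b and r are assumed, and they are taken as independent.

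Share of BT patients labelled as having a related event: L = 1 − (1 − b)(1 − r). Share of the labelled patients who had no BT reaction: (L − r)/L.

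| b | r | L | Labelled, of 260 | No BT reaction among labelled |
|---|---|---|---|---|
| 10% | 0 | 0.100 | 26 | 100% |
| 30% | 0 | 0.300 | 78 | 100% |
| 5% | 10% | 1 − 0.95 × 0.90 = 0.145 | 37.7 | 0.045/0.145 = 31% |
| 10% | 5% | 1 − 0.90 × 0.95 = 0.145 | 37.7 | 0.095/0.145 = 66% |
| 20% | 5% | 1 − 0.80 × 0.95 = 0.240 | 62.4 | 0.190/0.240 = 79% |
| 30% | 5% | 1 − 0.70 × 0.95 = 0.335 | 87.1 | 0.285/0.335 = 85% |

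For b between 5% and 30% and r between 5% and 10%, the share of labelled patients without a BT reaction runs from 31% to 85%.

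**The case against.** The best defence is that the damage is confined to one label. All events are recorded with severity, and there is a control cohort. This stands, and it rules out four stronger readings that a reader might infer.

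- *That the tolerability aim fails altogether.* It does not. Only event-level attribution is uninformative. All-cause data survive, and recorded events can be relabelled.
- *That the rule hides true reactions.* No post-start reaction goes unlabelled. True reactions are diluted among background events, and the error runs against BT, so the rule cannot produce a falsely reassuring related-event rate.
- *That controls can never have a related event, so the label merely repeats cohort membership.* This does not follow strictly. The second condition carries no limit on onset or cohort, so read literally it could catch a control event that resembles a known BT effect. That would be one more false attribution.
- *That a contrast with zero related events in controls proves the defect.* Untreated patients should have no BT-related events under any sound rule.

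It can also be said that 'or' is a slip for 'and', and that a condensed article may leave the allocation between drug and BT effects to the full protocol. The first may be true, but nothing in the article says so, and the sentence would still need correction. The second means that the lack of detail on drug effects is not itself an error. It does not rescue the rule, which is stated in full and makes temporal order sufficient.

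**Conclusion.** The rule is wrong as written. In the BT cohort the related-event rate equals the all-cause post-start rate. It overstates BT harm and says nothing about the relationship component of aim c. This follows from the wording alone and needs no assumed figure.

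The size of the overstatement cannot be known from the article. The 26 to 78 of 260 is an illustration under an assumed background risk of 10% to 30% with no true BT effect. The 31% to 85% range depends in addition on assumed true-reaction risks of 5% to 10% and on independence.

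The reach is limited to one component of a secondary aim. The primary outcome, the sample size, the efficacy analyses and the all-cause adverse-event data are untouched. The point should be corrected before any related-event rate is reported.

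**What to change.** 1. Replace the 'or' rule with one that requires both onset after BT start and a known or plausible BT effect.
2. State how a drug side effect is told apart from a BT effect, so that the relatedness sentence and the drug sentence that follows it no longer claim the same event.
3. Reclassify the events already recorded under the new rule.
4. Report all-cause adverse-event incidence by cohort alongside the related-event rate. State that this comparison is unrandomised and confounded, because controls are patients who refused BT. It is context for the related-event rate and does not correct for biased judgement.

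Cost: one changed sentence, one field for the causality judgement, and a pass through the existing records, which works only if onset and a description of each event were kept. The downside is some judgement by investigators who know the cohort. A change to how events are asked about may come too late, since the article gives November 2024 as the end of enrolment and June 2025 as the start of analysis. Relabelling does not depend on those dates.

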### Follow up

Following enrollment, each patient will be examined for 3 consecutive times; at baseline (T0), after 2 weeks (T1), and after 45 days (T2) (one month after the end of the cycle of the therapy for the BT Cohort) (Fig. 1). T0 and T1 visits will be carried out by the physician in the enrollment setting. The T2 visit will be carried-out by phone. The study will be considered concluded when all follow-up data for each patient will be collected.

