## Abstract

Balneotherapy (BT) is considered an effective, non-pharmacological approach, in the multimodal treatment of the Primary Fibromyalgia Syndrome (FS). However, the evidence of efficacy and tolerability of BT in FS is still limited. This is a prospective multi-center two-cohort observational study. The main aim will be the comparison of the Minimal Clinically Important Difference (according to Fibromyalgia Impact Questionnaire—FIQ) achievement in FS patients treated with BT vs standard care. Secondary objectives will be to assess: a) BT impact on pain, quality of life, anxiety and depression; b) the persistence of benefits in six weeks c) BT safety profile. All FS patients with a stable treatment in the past 3 months and a moderate to severe disease (FIQ score ≥ 39) will be enrolled after providing written informed consent. Patients will be divided into two Cohort: a) BT Cohort (i.e., BT in addition to standard care)—BTC; b) Control Cohort (i.e., only standard care)—SCC. There will be three assessments: baseline, two and six weeks (i.e., one month after BT end in BTC). At each of them the subject will fill in the following questionnaires: FIQ, VAS pain, Short Form Health Survey 16, State-Trait Anxiety Inventory and Center for Epidemiological Studies Depression Scale. We expect to observe a more relevant improvement of disease activity in BTC than in SCC. The positive effect may extend even to pain, quality of life, anxiety and depression. The short- and medium-term effects are likely to be similar, without any significant warning in terms of tolerability. Collected data, deriving from a large sample of patients, will provide a new insight of BT role in moderate to severe FS treatment. In particular, it will be possible to quantify the short and medium-term BT impact on disease activity and secondary symptoms related to FS.

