### Outcomes

#### Primary outcome

The primary outcome of the study will be the percentage of patients with a minimal clinically important difference (MCID), defined as a decrease of more than 14% in their FIQ-Total score, at 15 days (Bennett et al. 2009; García-López et al. 2024).

The FIQ is a self-administered questionnaire evaluating the impact of the disease in daily activities; the score ranges from 0 to 100, and higher scores indicate a greater impact of the disease (Table 1). A score lower than 39 is considered a mild impact, 39 to 59 is considered moderate, and greater than 59 is considered severe (Burckhardt et al. 1991). In the present study, we will use the Italian translated validated version (Sarzi-Puttini et al. 2003).

**Table 1 Tab1:** Description of tests which will be administrated

Test	Description
Fibromyalgia Impact Questionnaire (FIQ)	FIQ is a self-administered instrument composed of 10 items that measure fibromyalgia patient status, progress and outcomes. Each question is rated on a 4-point Likert-type scale
Visual Analogue Scale (VAS)	Unidimensional measure of patients’ pain intensity, used to record pain progression and compare pain severity between patients
Widespread Pain Index (WPI)	19-point checklist that assesses the presence of pain or tenderness in 19 specific areas of the body; each affected area receives one point
Short-Form Health Survey (SF-12)	Self-reported outcome measure assessing the impact of health on an individual's everyday life. It is often used as a quality of life measure
State-Trait Anxiety Inventory (STAI)	STAI is a test that measures two types of anxiety – state anxiety and trait anxiety. It consists of 40 self-report items on a 4-point Likert scale, with higher scores representing higher levels of anxiety
Centre for Epidemiologic Studies Depression Scale (CES-D)	Brief self-report questionnaire developed to measure depressive symptoms severity. The CES-D consists of 20 questions that ask about various symptoms of depression as they have occurred in the past week

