#### Secondary outcomes

##### Pain

Pain intensity will be evaluated by a Visual Analogue Scale (VAS), a 10-cm long line with the value 0 on the left indicating “no pain” and the value 10 on the right indicating the “worst imaginable pain” (Scott and Huskisson 1976).

Furthermore, we will consider as a secondary outcome, the Widespread Pain Index (WPI) that is a measure of the number of painful areas (score range = 0–19) on the patient’s body over the last week before the assessment (Wolfe et al. 2010).

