##### Anxiety

The anxiety will be evaluated by the State-Trait Anxiety Inventory (STAI): this a self-administered test with two independent scales (STAI T-Anxiety Scale or Form X-2 and STAI S-Anxiety Scale or Form X-1); each one includes 20 items. A high score on the STAI corresponds to a high level of anxiety symptoms. For the present study, we will use the Italian validated STAI (Spielberger et al. 1983; Lazzari and Pancheri 1980).

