##### Depression

The assessment of depression will be performed by the Italian validated version of Centre for Epidemiological Studies Depression Scale (CES-D) (Radloff 1977; Fava 1983). It is a self-administered 20 items questionnaire evaluating the frequency of depression symptoms in the previous week; scores range from 0 to 60, with high scores indicating greater depressive symptoms. Scores of 16 or above are considered at risk for clinical depression.

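### The 45-day visit is by phone while the first two are in person, so if the FIQ is taken on the call, the only persistence analysis (15 versus 45 days, balneotherapy cohort alone) cannot separate time from measurement mode

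*Protocol article*

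**What the plan says.** **Visits.** Under Follow up, "T0 and T1 visits will be carried out by the physician in the enrollment setting", and for day 45 "The T2 visit will be carried-out by phone".

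**Instruments.** Under Primary outcome, "The FIQ is a self-administered questionnaire evaluating the impact of the disease in daily activities". The STAI is described under Anxiety ("this a self-administered test with two independent scales") and the CES-D under Depression ("It is a self-administered 20 items questionnaire evaluating the frequency of depression symptoms in the previous week"). Under Pain, the VAS is "a 10-cm long line with the value 0 on the left indicating" no pain, with the worst imaginable pain at the right end.

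**Who completes them.** The Abstract, after listing the three assessments, says: "At each of them the subject will fill in the following questionnaires".

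**Aim and analysis.** One secondary aim is "the persistence of clinical efficacy over a six-week follow-up". The model for it is in the Statistical analysis plan, under Primary outcome. It is a binomial regression in the BT cohort only, with FIQ responder status (reduction above 14%) as response and time (15 or 45 days) as predictor. The random-effects models for VAS, SF-12, STAI and CES-D, under Secondary outcomes, have two time points, baseline and 15 days.

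**The concern.** The Abstract and the Follow up section do not fit together as written. A person cannot hand over a self-completed form, or mark a 10-cm line for later measurement, during a phone call. The article mentions no mailed form, electronic form or verbal substitute.

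The mismatch matters because of the analysis attached to it. If the FIQ at day 45 is obtained on the call, every 15-day value in the stability model is an in-person value and every 45-day value is a phone value. No patient has the other mode at either time, so covariate adjustment cannot separate them. The model also has no control cohort against which a common shift could be seen.

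The response is a dichotomy at a 14% reduction, so a uniform shift in score moves the patients near the cut across it. A shift caused only by mode could then be reported as benefit lost or benefit kept.

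**Working it through.** **1. The plan's own figure.** For 30% versus 45%, two-sided alpha 0.05 and power 90%, the pooled-variance formula without continuity correction gives 217 per group (power at 217: 0.900). This reproduces the Sample size section. The present point does not change it.

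**2. Which analyses compare a T1 with a T2 value?**

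| Analysis | Times used | Mode as written | Affected? |
|---|---|---|---|
| Primary: FIQ responders, BT vs control | baseline, 15 days | in person at both | No |
| FIQ stability, BT cohort only | 15 vs 45 days | in person, then phone | Yes, if the FIQ is taken on the call |
| VAS, SF-12, STAI, CES-D models | baseline, 15 days | in person at both | No; no T2 term |

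**3. How far could a mode shift move the responder rate?** Inputs:
- 45% responders in the BT cohort (Sample size section), assumed here to be the true rate at both 15 and 45 days, so that nothing is lost.
- Mean baseline FIQ B = 50 to 70 and SD of percentage change SD = 20 to 30. These are assumptions; the article gives neither.
- A mode shift of s FIQ points, positive when the phone reads lower (better). This is also an assumption.

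With a normal percentage change, the apparent rate at 45 days is

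P = Φ( Φ⁻¹(0.45) + 100·s / (B·SD) ), with Φ⁻¹(0.45) = −0.126.

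For B = 60, SD = 25 (15 FIQ points; the 14% cut is 0.14 × 60 = 8.4 points) and s = −2, the shift term is −200/1500 = −0.133, so P = Φ(−0.259) = 39.8%. For s = +2, P = Φ(0.008) = 50.3%.

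| Shift | B = 60, SD = 25 | Range over B 50–70, SD 20–30 |
|---|---|---|
| phone 5 points higher | 32.3% | 26.6% to 35.8% |
| phone 2 points higher | 39.8% | 37.2% to 41.3% |
| no shift | 45.0% | 45.0% |
| phone 2 points lower | 50.3% | 48.8% to 53.0% |
| phone 5 points lower | 58.2% | 54.5% to 64.6% |

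**4. Against the precision of the contrast.** With 217 patients and within-patient correlation ρ of responder status, the 95% half-width of the T1–T2 difference is 1.96·√(2·0.45·0.55·(1−ρ)/217). This is 9.4 percentage points at ρ = 0 and 5.1 at ρ = 0.7, before the planned Bonferroni correction, which would widen it. A 2-point shift (about 5 percentage points in the central case) is near the lower end of that range. A 5-point shift (about 13) exceeds it.

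**5. What a control comparison would do.** Suppose the true 45-day rates were 45% and 30%, and apply the same shift to both cohorts at B = 60, SD = 25. For control, Φ⁻¹(0.30) = −0.524.
- Phone 2 points higher: BT 39.8%, control Φ(−0.658) = 25.5%. The difference is 14.2 points (unrounded rates) and the ratio 1.56.
- Phone 2 points lower: BT 50.3%, control Φ(−0.391) = 34.8%. The difference is 15.5 points and the ratio 1.45.

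The true values are 15 points and 1.50. A common shift moves the between-cohort difference by less than 1 point, against about 5 for the within-BT rate. The cancellation is close but not exact, because equal shifts in points are not equal shifts in risk or in log risk.

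**The case against.** The best reply is that the Follow up section says only that the visit is by phone. It does not say that questionnaires are read aloud. The Abstract has the subject fill them in at each assessment, which includes T2. Both hold if the forms are completed at home and the phone is only the contact. This is a condensed article, and form logistics may sit in the full protocol or the timeline figure. That stands, and it makes the confounding conditional. It does not remove the need to say how the FIQ is obtained, because the one persistence model depends on it.

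Four stronger readings are tempting and not supported:
- **That the T2 forms are read out by an interviewer.** A reader might infer this from the phone visit, but it is nowhere stated.
- **That the VAS, STAI and CES-D persistence results are biased.** No T1–T2 model is specified for them; their models stop at 15 days. For these scales the issue is only whether T2 data are comparable with T0 and T1, chiefly how a 10-cm line is marked at a phone visit.
- **That the phone visit adds an unblinding problem.** Patients know their cohort at every visit, since controls are those who decline BT. This is not specific to T2.
- **That bias has been shown.** The figures above show what a shift would do, not that there is one. A 2-point shift would often be hard to tell from sampling error.

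It is also fair to object that a BT-versus-control contrast at 45 days answers a different question from within-cohort stability and carries the confounding of self-selected cohorts. That stands too, which is why the contrast needs the adjustment planned for the primary outcome.

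**Conclusion.** The point holds in a limited form. The Abstract and the Follow up section need reconciling. If the FIQ is taken by phone at T2, time and mode are fully confounded in the only specified persistence analysis. A shift of a few FIQ points could then imitate or hide loss of benefit: roughly 4 to 8 percentage points of responders for a 2-point shift and 9 to 20 for a 5-point shift. Those sizes rest on assumed baseline scores, SDs and shifts, a normal model and a constant true rate of 45%. The real size and direction are unknown from the article. The primary 15-day result and the sample size are not affected. This should be changed, but it does not threaten the main conclusion.

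**What to change.** 1. **Reconcile the Abstract with Follow up and state how each instrument is obtained at T2.** Preferably use the same self-completed forms, on paper (with the 10-cm line) or electronically, completed by the patient at day 45, with the call kept for reminders and adverse events. The cost is printing and postage or a form link, and some late or missing forms. Home completion still differs in setting from the clinic.
2. **Where only a call is possible, record the mode** for each patient and instrument, including what replaced the VAS line.
3. **In either case, extend the stability model to both cohorts** at 15 and 45 days with a time-by-cohort term, allowing for two observations per patient and using the same confounder adjustment as the primary model. Base the persistence conclusion on the BT-versus-control contrast at 45 days and report the within-BT change as descriptive. Follow up already takes both cohorts to T2, so this needs no new data, and it remains possible if data collection is complete.
4. **State the limit.** This removes a mode effect only if it is equal in both cohorts, and for a responder proportion only approximately if the equality is in FIQ points.
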